## 3. Discussion

As recommended in various societies [33], neonatal units must be designed taking into account the fundamental role of families, fostering the creation of a family room versus an open bay, obtaining friendlier, more intimate, and comfortable spaces for the family, incorporating neonatal care and promoting kangaroo care at any time, provided the neonate is stable. This requires validating alternative postures to the kangaroo care prone position as the baby will be in KC for long hours, and postural changes must be made to prevent possible complications as in traditional incubator care.

KC is endorsed by multiple studies, although scarce in the population of study of this paper, infants under 28 weeks of GA [17]. Furthermore, no studies have currently been found that analyze the effectiveness of alternative kangaroo positions other than prone kangaroo care, aiming to contribute evidence of the effectiveness of lateral position KC in terms of thermal stability and pain alleviation.

Meanwhile, we must determine the safety of the KC prone position in relation to increased intraventricular hemorrhage in premature under 28 weeks of GA during their first days of life, as evidence found is scarce and controversial [23].

The possible limitations of the study are as follows: (a) in terms of the study population, due to the immaturity of the premature infants, the sample size may be reached in a broad period of time caused as possible hemodynamic instability may not allow kangaroo care the first days of life; (b) regarding intervention, the first kangaroo care session may be delayed until approximately 20 h of life due to the numerous formalities required of the father, and as the mother is normally not available to act as kangaroo due to health issues as she is not admitted in the same room as the baby; (c) related to biased information as the data collection notebook is not fully filled in due to healthcare team workload, always guaranteeing the collection of dependent variables; (d) ultrasound sensitivity in early intraventricular hemorrhage detection; (e) the relatively small sample size for the IVH outcome. The sample size for this secondary outcome was not calculated due to the heterogenous literature available about IVH in relation to the risk that would be caused by the prone position compared with the other positions; and finally, (f) pain is measured on the validated PIPP-R scale but not validated in Spanish; there is currently no validated scale in Spanish for assessing neonatal pain. In addition, with regard to the assessment of pain, it will not be possible to blind the observers or to carry out the measurement of pain by two professionals independently.

These restrictions will be taken into account during data analysis, analyzing missing values, and, if necessary, completing simple imputation of these values.

## 4. Conclusions

This will be the first study contributing scientific evidence on modified kangaroo care lateral position as an alternative to conventional prone kangaroo care; we only found one study to evaluate the kangaroo supported diagonal flexion positioning on safety and early communication, but the sample size is limited, and the outcomes are different [34].

With greater parent participation in caring for their children in the NICU context, and based on scientific evidence, kangaroo care is ever more extended in frequency and duration, but neonate postural changes must be proposed, incorporating the practice of modified kangaroo care lateral position.

On the other hand, this study aims to provide evidence in relation to better positioning during the first days of life of extremely premature babies to prevent intraventricular hemorrhage related to neonate morbidity and mortality.

## Figures and Tables

**Figure 1 ijerph-19-00293-f001:**
[figure not shown]
Flow of participants.

**Table 1 ijerph-19-00293-t001:** Participant timeline. SPIRIT Schedule of enrolment, interventions and assessment.

	Activity/Assessment	Staff Member	Approximate Time to Complete	Before First Session Kangaroo Care	t_0_	t_1_	t_2_	t_2_’	t_3_	t_4_	t_5_
enrollement	Informed consent	Study coordinator/study staff	10 min	x							
	Inclusion/exclusion form	Study coordinator/study staff	2 min	x							
	Allocation	Study coordinator/study staff	1 min	x							
Intervention	Intervention A: Prone kangaroo care	Neonatal nurse	5 min								
	Intervention B: Lateral Kangaroo care	Neonatal nurse	5 min								
	Eco-TF	physician	5–10 min	x							
Assessment	neonatal axillary temperature	Neonatal nurse	<1 min		x	x	x	x		x	
	Score pain	Neonatal nurse	min		x		x	x		x	
	Eco- TF: Intraventricular hemorrhage (IVH)	physician	5–10 min	x							x
	mother/father axillary temperature	Neonatal nurse	10 seg		x		x	x	x		
	Incubator temperature	Neonatal nurse	1.5 min		x					x	
	Incubator humidity	Neonatal nurse			x					x	
	Heater temperature	Neonatal nurse			x		x	x		x	
	Heart rate	Neonatal nurse			x		x	x		x	
	Oxygen Saturation	Neonatal nurse			x		x	x		x	
	Fio2	Neonatal nurse			x		x	x		x	
	Apnea				x		x	x		x	
	Box temperature	Neonatal nurse	1 min		x		x	x		x	
	Box humidity	Neonatal nurse			x		x	x		x	
	Sound	Neonatal nurse			x		x	x		x	
	Light	Neonatal nurse			x		x	x		x	
	Activity inside the box	Neonatal nurse	2 min		x		x	x		x	
	Duration kangaroo care	Neonatal nurse	<1 min								
	days in NICU stay	Study coordinator	5 min								x
	days in the hospital	Study coordinator	5 min								x
	days on mechanical ventilation	Study coordinator	5 min								x
	Mortality at 6 month old	Study coordinator	5 min								x

t_0_: 10 min previous the kangaroo care. t_1_: 15 min after beginning the kangaroo care. t_2_: 30 min after beginning the kangaroo care. t_2_’: if the duration kangaroo care is longer than 60 min, It assessment each 60 min after beginning the kangaroo care, so, 120 min after beginning the kangaroo care; 180 min after beginning the kangaroo care, etc. t_3_: at finish the kangaroo care. t_4_: 30 min after finish the kangaroo care. t_5_: delivery.

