### 2.10. Outcomes

Primary outcome:
Premature infant axillary temperature.

Secondary outcomes:
Neonatal pain level.Intraventricular hemorrhage number of events.

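### Table 1 schedules no infant temperature at the end of kangaroo care, although the parent is measured then, and it is not reconciled with the continuous probe

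*Protocol article*

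**What the plan says.** Table 1 of the protocol article sets the assessment times within a session:

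- t0 is 10 min before KC.
- t1 is "15 min after beginning the kangaroo care" and t2 is "30 min after beginning the kangaroo care".
- t2' applies "if the duration kangaroo care is longer than 60 min, It assessment each 60 min after beginning the kangaroo care, so, 120 min", with 180 min given as the next example.
- t3 is the end of the session: "t_3_: at finish the kangaroo care".
- t4 is "30 min after finish the kangaroo care".

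The row "neonatal axillary temperature" is marked at t0, t1, t2, t2' and t4. The row "mother/father axillary temperature" is marked at t0, t2, t2' and t3, and it is the only row marked at t3.

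Elsewhere in the article:

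- Section 2.8 sets a 60-min minimum session. It says infant temperature is assessed during KC, with rechecks at 15-min intervals when a reading is below 36.5 °C. Session data go into the medical record and are later extracted to the study notebook.
- Section 2.11 says infant temperature is measured continuously by a fixed axillary probe and also taken with a hand-held thermometer.
- Section 2.10 names the primary outcome only as "Premature infant axillary temperature".
- Section 2.13 tests the variation in axillary temperature between groups and names no time points.

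**The concern.** The trial asks whether lateral KC keeps the infant as warm as prone KC, with a non-inferiority margin of 0.2 °C (section 2.5). The Introduction gives the reason for doubt: side-lying leaves less skin in contact with the parent. That disadvantage acts for as long as the position is held, so the value at the end of the session bears directly on the question. The published schedule sends a nurse to the pair at that moment to measure the parent, but not the infant.

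The next scheduled infant reading is t4. By then KC is over, and Table 1 again marks incubator temperature and humidity, which it otherwise marks only at t0. A t4 value therefore reflects the transfer back and the time in the incubator as well as any residue of the position. In a non-inferiority comparison, values taken when neither arm is in its position tend to make the arms look alike, which favours the new position.

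**Working it through.** **Is the blank at t3 real?** The infant temperature row has 12 cells against 12 header cells. Its marks fall under t0, t1, t2, t2' and t4. The parent row, matched in the same way, falls under t0, t2, t2' and t3. The blank is not a column shift.

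**How long is the stretch without a scheduled reading?** For a session of D minutes, gap = D − (time of the last scheduled in-KC reading), and t4 falls at D + 30 from the start. The wording of t2' allows two readings:

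- Reading A: t2' is 120, 180, … as in the worked examples.
- Reading B: t2' is every 60 min, so 60, 120, 180, …, for sessions longer than 60 min.

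| D (min) | A: last reading | A: gap | B: last reading | B: gap | t4 (min from start) |
|---|---|---|---|---|---|
| 60 | 30 | 30 | 30 | 30 | 90 |
| 61 | 30 | 31 | 60 | 1 | 91 |
| 75 | 30 | 45 | 60 | 15 | 105 |
| 90 | 30 | 60 | 60 | 30 | 120 |
| 119 | 30 | 89 | 60 | 59 | 149 |
| 120 | 120 | 0 | 120 | 0 | 150 |
| 150 | 120 | 30 | 120 | 30 | 180 |
| 179 | 120 | 59 | 120 | 59 | 209 |

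At exactly 60 min both readings agree: the last 30 of 60 min (50%) has no scheduled value. At 119 min the share is 89/119 = 75% under A and 59/119 = 50% under B. Over 61 to 119 min the gap runs from 1 min (B, 61 min) to 89 min (A, 119 min). A session that stops exactly at 120 or 180 min has an end value only because t2' happens to coincide with the end.

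**Which way would t4 act?** Let d be the between-arm difference during KC, d4 the difference at t4, and w the weight of t4 in the compared variable. The expected difference is (1 − w)·d + w·d4. It is closer to zero than d whenever w > 0 and d4 lies between zero and d. The article states neither w nor anything about d4, so the direction can be argued but the size cannot be computed.

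**The case against.** The strongest reply is the probe. Section 2.11 says the primary variable is measured continuously, section 2.8 says all sessions are monitored and recorded, and the limitations paragraph of the Discussion promises that the dependent variables will always be collected. Table 1 may show only when a nurse makes an entry. This stands in part: a reader might infer that the end of the session goes unrecorded, and the documents do not support that. They support only that it has no scheduled reading. But no section says the continuous trace is stored, summarised or used as the primary data, so the two descriptions still have to be reconciled.

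Three further inferences go too far:

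- That every session of 60 to 119 min has its last in-position reading at 30 min. This is certain only at exactly 60 min; beyond that it depends on t2'.
- That a true deficit of 0.3 °C shrinks to exactly the 0.2 °C margin. That figure needs an equal-weight mean of t1, t2 and t4 and no difference left at t4: (0.3 + 0.3 + 0)/3 = 0.2. No section describes such a mean. Section 2.5 speaks of the difference between positions, and section 2.8 of assessment during KC.
- That heat loss is largest late in the session. The Introduction places the greater risk at transfer and gives no time course for the effect of position. Readings soon after transfer therefore have their own rationale.

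It is also fair to say that an article may leave the exact definition of the primary variable to a fuller document. That omission alone is not the point. The point is the schedule that the article does fix.

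**Conclusion.** The point holds in a limited form. Table 1 fixes a schedule for the primary outcome with no infant reading at the end of the position, at a defined time when the parent is measured. The stretch of KC without a scheduled reading is 30 min for a 60-min session and 1 to 89 min for sessions of 61 to 119 min, the range reflecting session length and the ambiguity in t2'. These figures assume only that Table 1 is followed as written.

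Table 1 is not reconciled with continuous measurement, and sections 2.10 and 2.13 do not confine the comparison to in-position values. A pull towards non-inferiority from t4 values is possible, but it is conditional on their being used and its size is unknown. The documents do not show that the planned analysis is biased. This is a cheap improvement to what the trial measures, and it does not by itself threaten the trial's validity.

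**What to change.** 1. Mark infant axillary temperature at t3 in Table 1, read from the probe already in place. Every session then has a scheduled value at the end of the position, and the gap falls to 0 min under either reading of t2'.
2. State whether t2' includes a 60-min reading for sessions longer than 60 min.
3. Reconcile Table 1 with section 2.11: say whether the continuous trace is stored, and whether the scheduled values come from the probe or from the hand-held thermometer.
4. Base the primary comparison on in-KC readings (t1, t2, t2', t3), with t0 as baseline covariate, and report t4 separately as recovery.

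The cost is one extra reading per session, which Table 1 puts at under 1 min, at a time when the nurse is already measuring the parent, plus edits to the table and the logbook. The pain score is also unmarked at t3, but Table 1 gives no usable duration for it and no case for adding it is made here.

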## Data Availability

Data not available due to privacy and copyright protection.

## Abbreviations

GA	Gestational age
IVH	Intraventricular hemorrhage
KC	Kangaroo care
NICU	Neonatal intensive care unit
NIDCAP	Newborn Individualized Developmental Care and Assessment
PIPP-R	Premature Infant Pain Profile-Revised
